#### Study 1: elderly cohort study for LTC need risk stratification

This study is a prospective cohort study that investigates the predictive ability of the KCL and the cognitive domain therein for incident LTC certification. The target group was approximately 80 000 elderly Kobe citizens to whom KCL was sent in 2015.

Inclusion: The general population will be eligible for inclusion if they are aged 70 years or older, responded to the KCL of 2015, and were not LTC need certified at the time of the KCL data collection.

A total of 77 900 target population with an estimated response rate of 60%, thus, 50 000 people are expected to participate in the study. The primary outcome is to be certified for LTC need. The secondary endpoints include levels (1–5) and causes (dementia or physical disability) of LTC need. The KCL data are collected via postal mail survey by the Kobe municipal office, which will be merged with LTC need certification data. The follow-up duration is calculated from the date of first response to KCL to the date of LTC need certification until a cut-off date of November 2019 (4 years).

For the statistical analysis, the incidence of LTC need at 1, 2, 3 and 4 years after KCL distribution will be estimated using the Kaplan-Meier method. For the estimation, data for all eligible citizens will be included in the time-to-event analysis. The follow-up duration is calculated from the date of first response to KCL to the date of LTC need certification up until a cut-off date of November 2019.

Subsequently, multivariate Cox regression analysis will be performed using the stepwise variable selection method to narrow down independent variables and to estimate the associated HR. Multivariate Cox Regression Analysis will be performed for 27 variables; age, sex and 25 questions of the KCL. Statistical analysis will be carried out using the SAS V.9.3 (SAS Institute). The significance threshold is set at p<0.05.

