#### Study 2: quantifying the risk of LTC need in citizens with possible cognitive decline

This is a prospective cohort study which examines the predictive ability of CFI and EQ-5D questionnaires, for LTC certification, in elderly citizens at higher risk of dementia. The sample population is a subgroup population of those that responded to the KCL of 2015 (a subgroup of study 1). The target population are those that responded with unfavourable answers to either of the three cognitive domain questions in the KCL from the 2015 survey. The major inclusion criteria are citizens who are above or equal to 70 years old at the time of KCL survey, had at least one unfavourable answer to the cognitive domain questions in the KCL, those that responded to CFI and EQ-5D questionnaires in 2017 and 2019, and are not LTC certified. The target population is 4131 citizens which were sent CFI, and EQ-5D in 2017. Out of which 2981 citizens responded. In 2019, this same cohort were sent the CFI and EQ-5D, out of which 2444 citizens replied. After discounting for uncompleted forms, 2292 formed the sample for this study. The primary endpoint is the occurrence of LTC need certification after 2 years, and the secondary endpoints are the change in CFI and EQ-5D during the same period. After matching for LTC certification, statistical analysis will be carried out with the use of proportional Hazard model. Relative risk for future LTC need and death is estimated in relation to the baseline CFI and EQ-5D. The relationship between the changes in such parameters and LTC need will also explored. Repeated measure analysis of variance (ANOVA) or mixed effect model will be used to examine the changes of CFI and EQ-5D, in relation to occurrence of LTC need.

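### Study 1 fixes Kaplan-Meier for 1–4 year LTC incidence at age 70+ without saying how deaths enter, so either the incidence is overstated or the hazard ratios change meaning

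*Protocol article*

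**What the plan says.** The Study 1 section of the protocol article enrols people "aged 70 years or older, responded to the KCL of 2015, and were not LTC need certified" when the KCL data were collected. No upper age limit is given.

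- **Estimator.** "the incidence of LTC need at 1, 2, 3 and 4 years after KCL distribution will be estimated using the Kaplan-Meier method".
- **Follow-up rule**, given twice in almost the same words: "The follow-up duration is calculated from the date of first response to KCL to the date of LTC need certification up until a cut-off date", which is set at November 2019.
- **Analysis set.** "data for all eligible citizens will be included in the time-to-event analysis".
- **Linkage.** The KCL data are those "which will be merged with LTC need certification data". No death or residency record is named.
- **Regression.** "multivariate Cox regression analysis will be performed using the stepwise variable selection method", on age, sex and the 25 KCL items.

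Death appears only in Study 2, whose sample is a subgroup of Study 1: "Relative risk for future LTC need and death is estimated" there in relation to baseline CFI and EQ-5D.

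**The concern.** A citizen who dies before certification can never be certified, so over four years in a cohort aged 70 and over death is a competing event for the primary outcome. The section chooses the estimator and writes the follow-up rule, but leaves this event out of both. Two analysts could follow the same text and report different quantities under the same name.

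If deaths are censored, one minus Kaplan-Meier is the risk in a population where nobody dies first, not the share of citizens who will be certified. The gap grows with mortality, so it is probably widest in the frailest group. If the dead are left at risk to the cut-off, the incidence is right, but the regression no longer describes the rate of certification among people still alive.

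The Meaning of study section wants limited public resources directed to people at risk. For that use, the reader needs to know which risk and which hazard ratio is being reported.

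**Working it through.** Study 1 states no mortality, event count or effect size, so there is no figure of the plan to reproduce on this point. The size has to be shown under assumptions.

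**Formulas.** Constant hazards, h1 for LTC certification and h2 for death without certification:

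- Kaplan-Meier with deaths censored: 1 − exp(−h1·t)
- Actual cumulative incidence (CIF): h1/(h1+h2) × [1 − exp(−(h1+h2)·t)]

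**1. Incidence if deaths are censored.** Assume h1 = 0.03 a year and t = 4. Then 1 − exp(−0.12) = 11.3%, whatever the death rate.

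| Assumed h2 per year | CIF at 4 years | Result | Relative overstatement |
|---|---|---|---|
| 0.02 | 0.03/0.05 × (1 − exp(−0.20)) | 10.9% | 4% |
| 0.04 | 0.03/0.07 × (1 − exp(−0.28)) | 10.5% | 8% |
| 0.08 | 0.03/0.11 × (1 − exp(−0.44)) | 9.7% | 16% |

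**2. The same, by risk group.** The Discussion gives 3-year LTC incidences of 3.5, 6.4, 12.6 and 29.6% for 0, 1, 2 and 3 unfavourable cognitive answers, from a prior retrospective analysis. Read these as Kaplan-Meier with deaths censored (an assumption), so h1 = −ln(1 − p)/3. Assume annual mortality of 2, 3, 5 and 10% in the four groups, so h2 = −ln(1 − mortality).

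| Unfavourable answers | 3 years: KM | 3 years: CIF | 4 years: KM | 4 years: CIF |
|---|---|---|---|---|
| 0 | 3.5% | 3.4% | 4.6% | 4.5% |
| 1 | 6.4% | 6.1% | 8.4% | 8.0% |
| 2 | 12.6% | 11.7% | 16.4% | 14.9% |
| 3 | 29.6% | 25.6% | 37.4% | 31.0% |

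The error is 0.1 point at 3 years in the lowest group. In the highest it is 4.0 points at 3 years and 6.4 points at 4 years. The top-to-bottom 3-year risk ratio is 8.5 by Kaplan-Meier and 7.5 by CIF. The order of the groups is the same.

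**3. Incidence if the rule is applied literally.** Everyone not certified, dead or alive, is event-free to the cut-off, which is then the only censoring. A simulation of 400,000 people per group, same hazards, cut-off spread over 3.9 to 4.1 years, gave 3-year Kaplan-Meier values of 3.4, 6.2, 11.7 and 25.7%. The true CIF is 3.4, 6.1, 11.7 and 25.6%. Death does not bias the incidence on this reading.

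**4. Hazard ratios under each reading.** With deaths censored, the Cox model estimates the cause-specific ratio. With the dead kept at risk it estimates a subdistribution-type ratio, approximated here by the ratio of −ln(1 − CIF). Assume a factor that doubles LTC from 0.02 to 0.04 a year (cause-specific ratio 2.0), with t = 4:

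- Reference, death 0.03: CIF = 0.4 × (1 − exp(−0.20)) = 0.0725, and −ln(1 − 0.0725) = 0.0753.
- Death also doubled, 0.06: CIF = 0.4 × (1 − exp(−0.40)) = 0.1319, and −ln(1 − 0.1319) = 0.1414. Ratio 0.1414/0.0753 = 1.88.
- Death tripled, 0.09: CIF = 0.04/0.13 × (1 − exp(−0.52)) = 0.1248, and −ln(1 − 0.1248) = 0.1333. Ratio 0.1333/0.0753 = 1.77.

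In the groups of step 2, at 3 years, 3 against 0 unfavourable answers gives about 9.9 cause-specific and 8.6 subdistribution-type.

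**The case against.** The strongest reply is that the written rule, taken at its word, gives the right incidence. It does not say that deaths are censored, and with the dead event-free to November 2019 Kaplan-Meier equals the cumulative incidence. The subdistribution-type ratio that follows is a recognised quantity for prediction. If deaths are censored instead, the Cox ratios are the ones recommended below. All of this stands. A reader might infer that both the risks and the ratios are distorted, but neither reading does that.

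A reader might also infer that the risk stratification itself fails. The assumed scenario does not show this: the groups keep their order, and the section announces no calibrated prediction model and no stratified curves.

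A third inference would be that the secondary endpoint by cause of LTC need (dementia or physical disability) has the same flaw. The section names that endpoint but no analysis for it, so there is nothing to criticise there.

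It can further be said that an article condenses the full protocol, and that Study 2 shows deaths are in view, so silence does not prove that deaths are unavailable or unhandled. That is fair as to availability. It does not answer the point on method: the article itself names the estimator and twice states when follow-up ends, and those two statements do not determine one result.

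Finally, no mortality figure stands in the documents, and at 2% a year the example error is only 0.4 point over 4 years (11.3 against 10.9%). That also stands.

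**Conclusion.** The point holds in conditional form. Study 1 fixes Kaplan-Meier and a follow-up rule that omits a competing event, and what is then reported depends on an unstated choice.

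- **Deaths censored:** incidence is overstated, by 4 to 16% in relative terms at 4 years for assumed death hazards of 2 to 8% a year and LTC at 3% a year. The error is largest where mortality is highest. The hazard ratios are valid cause-specific ratios.
- **Dead kept at risk to the cut-off:** death does not bias the incidence. The hazard ratios mix effects on LTC and on mortality, about 1.9 instead of 2.0 in the example.

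These sizes rest on constant hazards and assumed mortality; the direction does not depend on the exact values. The change is worth making because it is specific and cheap, and it gives correct incidence together with clearly defined ratios.

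There is a separate wording mismatch: incidence is quoted from distribution of the KCL, while time is counted from first response. It has nothing to do with competing risk, and its effect cannot be sized from the document.

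**What to change.** 1. Link date of death to the Study 1 records, and date of move out of Kobe if the municipality holds it. State in the follow-up rule how each is handled.
2. Report LTC incidence at 1, 2, 3 and 4 years by the Aalen-Johansen cumulative incidence function, with death as the competing event and move-out as censoring.
3. Fit the Cox models with censoring at death, move-out or the cut-off, and label the hazard ratios cause-specific.
4. Count time from the date of first response in both the incidence sentence and the follow-up rule.

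The cost is one extra record linkage and a few lines of analysis wording. Study 2 already plans to estimate the risk of death in a subgroup of this cohort; whether dates of death are held for all of Study 1 is not stated and needs confirming. The reported incidences will be slightly lower than one minus Kaplan-Meier with deaths censored.

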#### Kihon Check List

KCL is a self-reported frailty questionnaire designed by the MHLW, to identify frail elderly individuals at risk for LTC. The questionnaire used can be found in online supplemental file 1. It consists of a 25-item self-reported questionnaire and has been widely delivered to citizens from local governments across the nation from 2006 to 2016. It covers several domains of instrumental activities for daily living (ADLs), including general independence, physical strength, nutritional status, oral function, housebound, cognitive function, depression risk and general health status. In particular, the KCL includes three cognitive function-related questions—Do your family or your friends point out your memory loss? Do you make a call by looking up phone numbers? Do you find yourself not knowing today’s date?

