First the incidence of LTC over the study period will be calculated using LTC care level 1 or greater. The statistical methods to be used are logistic regression model (estimated by least absolute shrinkage and selection operator: LASSO) with the presence and absence of LTC care as the dependent variable with CFI Self score, EQ-5D scores and other ‘Frail Kenshin’ check-up results as explanatory variables. A formula and Receiver Operatorating Characteristic (ROC) curve will be estimated. Multiple regression will also be carried out for continuous variables used in the ‘Frail Kenshin’ health check-up. In addition, age and gender are included in the model as explanatory variables in all analysis. In the case that the significance level of the above-mentioned test is p<0.05 on both sides, the multiplicity of the tests is not considered an issue. SAS V.9.4 and R V.3.6 are used for the analysis.

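### Study 1 sets out to measure the predictive ability of the KCL and its cognitive domain, but its stepwise Cox analysis assesses neither the domain as a unit nor prediction; Study 3's sentence on multiplicity also needs rewording

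*Protocol article*

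**What the plan says.** **Study 1.** The aim has two parts, the KCL as a whole and its cognitive domain: the study "investigates the predictive ability of the KCL and the cognitive domain therein for incident LTC certification". The section Kihon Check List says that "the KCL includes three cognitive function-related questions", so the domain is three of the 25 items.

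Two analyses are stated. First, "the incidence of LTC need at 1, 2, 3 and 4 years after KCL distribution will be estimated using the Kaplan-Meier method". Second, "multivariate Cox regression analysis will be performed using the stepwise variable selection method to narrow down independent variables and to estimate the associated HR". The candidates follow: "Multivariate Cox Regression Analysis will be performed for 27 variables; age, sex and 25 questions of the KCL". The criterion is brief: "The significance threshold is set at p<0.05". No domain score, count or joint test is named, and no measure of discrimination or calibration. Age and sex are listed with the other candidates, and nothing says that they are forced into the model.

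**Study 3.** The analysis is a LASSO logistic regression for LTC need. A formula and an ROC "curve will be estimated". Age and gender are in the model in all analyses. The section then says that, at a two-sided p<0.05, "the multiplicity of the tests is not considered an issue".

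**The concern.** A stepwise Cox model shows which single items keep a p-value below 0.05 once the other retained items are in the model. That is a different question from how well the KCL, or its cognitive domain, separates people who will need LTC from those who will not. One or two cognitive items may be retained and the others replaced by correlated items from other domains, and the report would then contain no estimate for the domain. The hazard ratios come from the same step that selected the variables.

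The Discussion reports a prior analysis of 182,099 Kobe citizens that already found unfavourable cognitive answers associated with LTC need, independent of age, sex and the other KCL items. More adjusted hazard ratios would largely repeat that result. What the Discussion says the present project adds is a test of predictive ability, and the stated analysis lacks a measure of it. The results are meant to help direct support to high-risk citizens, so the omission matters.

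In Study 3, the sentence on multiplicity gives a reason that does not hold, in a study that sets out to search for further prognostic factors.

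**Working it through.** **1. Aim against analysis, Study 1**

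| The aim asks for | The stated analysis gives |
|---|---|
| Predictive ability of the KCL | Overall incidence at 1 to 4 years; hazard ratios of retained items |
| Predictive ability of the cognitive domain | Three separate candidates, each kept or dropped singly |
| A basis of age and sex to improve on | Age and sex as candidates (in Study 3 they are always included) |

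**2. The planned sample size.** Study 1 gives a target of 77,900 and a 60% response: 77,900 × 0.60 = 46,740, not the stated 50,000. This is a separate arithmetic point. Table 1 gives a sample of 50,155, which is used below; step 3 shows that the conclusion is the same with 46,740.

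**3. Is selection needed in Study 1?** The article gives no incidence for this cohort. The Discussion gives prior 3-year incidences of 3.5%, 6.4%, 12.6% and 29.6% for 0, 1, 2 and 3 unfavourable cognitive answers. Applying the lowest to everyone is a cautious assumption, since follow-up here runs to about 4 years.

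- Events = 0.035 × 50,155 = 1,755; per candidate, 1,755 / 27 = 65.
- With 46,740 people: 0.035 × 46,740 = 1,636; 1,636 / 27 = 61.
- At an assumed 4-year incidence of 5% to 15%: 2,508 to 7,523 events, or 93 to 279 per candidate.

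The full 27-variable model can be estimated without selection.

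**4. What does surviving p<0.05 show?** By Schoenfeld's formula, power = Φ(√(D·p(1−p))·|ln HR| − 1.96). Assume 10% incidence (D = 5,016 events) and an item answered unfavourably by p = 20%: √(5,016 × 0.16) = 28.33.

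- HR 1.10: 28.33 × 0.0953 − 1.96 = 0.74, power 77%.
- HR 1.15: 28.33 × 0.1398 − 1.96 = 2.00, power 98%.

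An item with a weak effect is likely to be retained, so retention says little about predictive value.

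**5. The multiplicity sentence, Study 3.** A level of 0.05 is an error rate for one test. For k independent true null hypotheses, the chance of at least one p<0.05 is 1 − 0.95^k: 64% for k = 20 and 72% for k = 25. The number of tests is not given and frailty measures are unlikely to be independent, so these figures only illustrate the principle. The sentence also refers back to a test that the section has not defined: LASSO gives no standard p-value.

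**6. Conditional check, Study 3 ROC curve.** This applies only if the curve is computed on the data that built the formula, with no validation. Simulation assumptions: N = 2,705, 30 independent predictors, incidence 0.5% to 3% (about 14 to 81 events), penalty by 5-fold cross-validation, 25 runs per setting. With five true effects (log odds ratio 0.35 per SD), mean AUC on the same data against new data was 0.69 against 0.55 at 0.5% incidence, and 0.74 against 0.67 at 3%. Over these settings and those with no true effects, the overstatement was about 0.05 to 0.14. The article gives none of these inputs except N.

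**The case against.** **The cognitive items are in the model.** All three are candidates, and with some 50,000 people and the strong gradient in the prior analysis, losing the whole domain is unlikely. This stands: a reader might infer that the cognitive questions go unexamined, and that is not so. What remains is that the domain has no estimate or test of its own.

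**Overfitting in Study 1.** A reader might infer that selection and estimation on the same data seriously distort the Study 1 results. The events per variable in step 3 speak against that.

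**Study 3 validation.** A reader might infer that the ROC curve will be an apparent one and will overstate discrimination. The article does not say whether it is apparent, cross-validated or tested elsewhere, and an article may leave that to the analysis plan. LASSO also shrinks coefficients. The objection stands, so this part is conditional.

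**Study 3 is worded as an exploration.** Openly unadjusted testing is common in such work, and the sentence may mean no more than a two-sided 5% level without adjustment. That softens the point but does not rescue the reasoning: the level used for each test does not remove multiplicity. The Abstract also calls only Study 4 purely exploratory.

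**Scope.** The point does not extend to Study 2, which names CFI and EQ-5D in advance and states no selection step.

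**Conclusion.** The point holds for Study 1 as a mismatch between aim and analysis. The stated stepwise Cox model has no domain-level term and no measure of prediction, and selection has no purpose at 65 or more events per candidate. That figure assumes that the lowest prior 3-year incidence, 3.5%, is a fair lower bound for this cohort; higher incidence strengthens it. The power figures further assume 10% incidence and 20% item prevalence.

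For Study 3, the sentence on multiplicity is not valid as reasoning and refers to an undefined test; this is a matter of wording. No claim is made that the Study 3 AUC will be inflated. That depends on whether validation is planned and, for its size, on event rates, predictor counts and effects that the article does not give.

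**What to change.** **Study 1.** Drop stepwise selection. Fit one pre-specified Cox model with age, sex and the 22 KCL items outside the cognitive domain, then add the domain. It can enter as the three items jointly or as the 0 to 3 count used in the Discussion; the count is simpler but gives the items equal weight, so choose in advance. Report the joint test of the domain, the gain in C-index or time-dependent AUC, and calibration at 1, 2, 3 and 4 years.

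**Study 3.** Replace the multiplicity sentence with a statement that single-factor tests are unadjusted and exploratory, and name the tests meant. If no internal validation is already planned, report an optimism-corrected or cross-validated AUC with the selection repeated in each resample.

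**Cost.** No new data are needed. There is slightly more analysis work and some rewording, and the reported figures may look less favourable.

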#### Study 2: quantifying the risk of LTC need in citizens with possible cognitive decline

This is a prospective cohort study which examines the predictive ability of CFI and EQ-5D questionnaires, for LTC certification, in elderly citizens at higher risk of dementia. The sample population is a subgroup population of those that responded to the KCL of 2015 (a subgroup of study 1). The target population are those that responded with unfavourable answers to either of the three cognitive domain questions in the KCL from the 2015 survey. The major inclusion criteria are citizens who are above or equal to 70 years old at the time of KCL survey, had at least one unfavourable answer to the cognitive domain questions in the KCL, those that responded to CFI and EQ-5D questionnaires in 2017 and 2019, and are not LTC certified. The target population is 4131 citizens which were sent CFI, and EQ-5D in 2017. Out of which 2981 citizens responded. In 2019, this same cohort were sent the CFI and EQ-5D, out of which 2444 citizens replied. After discounting for uncompleted forms, 2292 formed the sample for this study. The primary endpoint is the occurrence of LTC need certification after 2 years, and the secondary endpoints are the change in CFI and EQ-5D during the same period. After matching for LTC certification, statistical analysis will be carried out with the use of proportional Hazard model. Relative risk for future LTC need and death is estimated in relation to the baseline CFI and EQ-5D. The relationship between the changes in such parameters and LTC need will also explored. Repeated measure analysis of variance (ANOVA) or mixed effect model will be used to examine the changes of CFI and EQ-5D, in relation to occurrence of LTC need.

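### Study 2 requires a 2019 questionnaire reply for entry, so eligibility for the primary LTC analysis is decided at the end of its own 2017–2019 outcome window

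*Protocol article*

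**What the plan says.** All of this is in the Study 2 section of the protocol article.

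- **Inclusion.** Besides age and an unfavourable cognitive answer in the 2015 Kihon Check List, the criteria admit "those that responded to CFI and EQ-5D questionnaires in 2017 and 2019, and are not LTC certified". The certification condition carries no date.
- **Participant flow.** The rule was applied. Forms went to 4131 people in 2017 and 2981 came back. For the second wave the article states: "In 2019, this same cohort were sent the CFI and EQ-5D, out of which 2444 citizens replied". Removing incomplete forms left an analysed sample of 2292.
- **Primary endpoint.** "The primary endpoint is the occurrence of LTC need certification after 2 years". The secondary endpoints, change in CFI and EQ-5D, are assigned to that same period. Table 1 gives Study 2 a study period of 2 years.
- **Analysis.** A proportional hazards model is planned after linkage to certification data. "Relative risk for future LTC need and death is estimated in relation to the baseline CFI and EQ-5D". The association between change in the scores and LTC need is also to be explored, by repeated-measures ANOVA or a mixed model.

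The LTC certification section says that certification is made routinely by the municipal office on application. The outcome can therefore be known without a 2019 questionnaire.

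**The concern.** The predictors are measured in 2017 and the outcome accrues from 2017 to 2019. Membership of the cohort is fixed only when a person does or does not reply in 2019. That reply comes after baseline and can itself be affected by the outcome: the dead cannot reply, and people newly in need of care are probably less likely to complete a self-report form. The LTC certification section places severely disabled communication at the top of the care scale.

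Two results are at stake. One is the absolute LTC risk that Study 2 is meant to quantify, together with its relation to CFI and EQ-5D. The other is the relative risk of death, which the plan promises but which a sample restricted to 2019 repliers cannot supply over that window. The loss is self-imposed, because the primary outcome comes from records and not from the second form.

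**Working it through.** The article states no sample size, power or event count for Study 2, so there is no calculation of its own to reproduce. The check uses the stated flow and then illustrates the effect under labelled assumptions.

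**1. Flow (Study 2 section)**
- Replied in 2019, as a share of 2017 responders: 2444/2981 = 82.0%. Difference: 2981 − 2444 = 537 (18.0%).
- Further loss to uncompleted forms: 2444 − 2292 = 152.
- Analysed: 2292/2981 = 76.9%. Not analysed: 2981 − 2292 = 689 (23.1%).

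The split into 537 and 152 is not firm. The 2019 mailing may have gone to the 2981 responders or to all 4131 citizens. In the second case the 2019 reply rate is 2444/4131 = 59.2%, and 537 is the minimum number of 2017 responders who did not reply. The article also does not say which wave the uncompleted forms came from. Table 1 gives the sample as 2385 and not 2292, a difference of 93 that needs reconciling separately. With 2385 the loss would be 2981 − 2385 = 596 (20.0%).

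**2. Deaths**
A person who dies before replying in 2019 fails the inclusion rule, so the sample contains 0 deaths between baseline and the 2019 reply. The article gives no mortality figure. At an assumed 2-year mortality of 3% to 8%, 2981 × 0.03 ≈ 89 to 2981 × 0.08 ≈ 238 deaths would be excluded.

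**3. LTC incidence (illustration)**
Assume a true 2-year risk of 6%. The Discussion quotes 3-year incidences of 6.4% and 12.6% for one and two unfavourable cognitive answers in a prior study. With a constant hazard, 1 − (1 − p)^(2/3) gives about 4.3% and 8.6% at 2 years, so 6% lies between them. Let f be the share of certified people who return complete forms:

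observed risk = 2981 × 0.06 × f / 2292 = 178.9 × f / 2292

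| f | Events kept | Observed risk |
|---|---|---|
| 0.70 | 125 | 5.5% |
| 0.50 | 89 | 3.9% |
| 0.30 | 54 | 2.3% |

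The observed risk equals 6% only when f equals the overall 76.9%, that is, when certified people return complete forms as often as everyone else.

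**4. Association with CFI or EQ-5D (illustration)**
Assume true risks of 12% (worse score) and 4% (better score), a relative risk of 3. In each group:

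observed risk = risk × e / (risk × e + (1 − risk) × n)

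where e and n are the return fractions among those with and without an event.

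- e = 0.60 in both groups, n = 0.80 (worse) and 0.88 (better): 9.28% / 2.76% = 3.36.
- e = 0.60 in both groups, n = 0.85 in both: 8.78% / 2.86% = 3.07.
- e = 0.30 (worse) and 0.70 (better), n = 0.85 in both: 4.59% / 3.32% = 1.38.

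Across the patterns tried, the true value of 3 became 1.4 to 3.4. The bias can run either way.

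**The case against.** The strongest defence is that two questionnaires are needed to measure change, and change is a declared endpoint. That stands for the secondary endpoint. It does not explain why the rule is an inclusion criterion for the whole study.

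A second defence is that follow-up might start in 2019, which would make the rule harmless. The abstract does mention follow-up of up to 4 years for Studies 1 to 3, and the studies are described as ongoing. Against that, the Study 2 section puts the primary endpoint and the score changes in the same 2 years, names the baseline scores as predictors, and Table 1 gives 2 years.

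A reader might also infer several stronger things that the document does not support:

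- **That the cohort must have stayed well, or that every LTC event is removed.** A certified citizen can still return a form, so events are probably depleted but not excluded. The undated certification condition would remove all events only if applied in 2019. Studies 1 and 3 both date it to baseline, and incident certification is Study 2's own endpoint, so baseline is the natural reading. A date would settle it.
- **That the hazard ratios are attenuated.** Selection on the outcome alone leaves an odds ratio unchanged, and other patterns push a ratio up. Nothing in the article fixes the direction.
- **That the change analysis is invalid.** The ANOVA or mixed model treats change as the dependent quantity, which does not require change to precede certification. A problem of order arises only if change is used to predict events that came before the 2019 form.
- **That death can never be studied.** The gap concerns 2017–2019. Later deaths could be observed, but no later follow-up is stated for Study 2 and no source of death data is named.

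**Conclusion.** The point holds as stated in the heading. It follows from the text alone that eligibility is decided at the end of the outcome window, that deaths before the 2019 reply are excluded, and that the promised relative risk of death has no events over 2017–2019. The analysed sample is 76.9% of baseline responders. Up to 689 people (23.1%) are lost to the rule, fewer if some of them had incomplete 2017 forms or were already certified.

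Understatement of LTC incidence is probable but not certain. It rests on the assumption that newly certified people complete the 2019 form less often than others. The figures of 5.5%, 3.9% and 2.3% against 6% show the scale under assumed return rates and do not estimate the actual bias. For the CFI and EQ-5D hazard ratios, only the possibility of bias can be asserted. Because the rule affects the primary endpoint and empties a stated analysis, it should be corrected before Study 2 is analysed.

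**What to change.** 1. Define the primary cohort as all citizens with completed 2017 CFI and EQ-5D forms who were not LTC certified on the 2017 response date.
2. Follow all of them in the municipal certification records from that date, whether or not a 2019 form was returned. Where death data are available, censor at death or treat it as a competing event.
3. Confine the two-questionnaire requirement to the secondary analysis of change in CFI and EQ-5D. If change is used as a predictor of LTC need, relate it only to certifications after the 2019 response.
4. Estimate the relative risk of death only in the 2017 baseline cohort and only if death data can be obtained; otherwise drop it.

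The cost is revised wording and extra linkage for up to about 690 people to certification records that the municipality already keeps. No new questionnaires are needed. Access to death data is not described in the article and would have to be confirmed.
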